### Health economic analysis

A cost analysis will be performed in order to compare the cost per patient in each treatment group. Data relating to patients’ primary hospital admission is collected prospectively until primary hospital discharge (including but not limited to their length of stay on a ward and in the intensive care unit). Data relating to readmissions, accident and emergency attendances, and outpatient attendances will be collected at the *t*_5_ visit. Unit costs will be obtained from public sources, e.g., Department of Health reference costs. The differences in costs between the groups will be estimated using regression methods adjusted for baseline and other covariates where appropriate.

## Discussion

### Blood loss

One of the greatest risks of any technical demanding surgical procedure is bleeding. It is similar to radical prostatectomy. The robot-assisted approach leads to a significant reduction of blood loss. Nevertheless, efforts to reduce the blood loss even more are eagerly awaited. Perioperative hemorrhage makes the surgical terrain unclear, makes it difficult to dissect the tissue precisely, increases the risk of complications, and worsens functional and oncological results. Excellent experience in orthopedics and other cardio-surgical fields with the prophylactic administration of tranexamic acid after the introduction to anesthesia gives rise to the hope of successful use in urology as well.

We decided not to estimate perioperative blood loss visually, because of its inaccuracy and unreliability documented by Rothermel et al. [9]. The cause lies in many biases as we confirmed in our pilot study [29]. The volume of suction fluid is affected by urine coming out of the open urinary tract with different intensities for various lengths of time and by variable lymphatic secretion from damaged tissue.

Therefore, we focused on the drop in hemoglobin levels. Chesnut et al. in their retrospective evaluation of 3631 patients found a median decrease in hemoglobin 4 h after the procedure by 11 g/l and 14 h after the procedure by 20 g/l [36]. In our pilot study, we found average hemoglobin level drop 3 h after the procedure by 9.3 g/l vs. 17.3 g/l. On POD 1, it was 17.6 g/l vs. 25.6 g/l in favor of the study group. The average difference between the study and control groups was 8 g/l in both measurements if the dorsal vein complex was sutured at the beginning of the procedure. We considered the difference to be promising and set the level of significance in sample size calculations to 10 g/l.

A decrease in hemoglobin level by 30% or 40 g/l or need for blood transfusion was reported in the literature as clinically significant blood loss [37]. Considering these data, the difference of 10 g/l may seem insufficient. However, on the other hand, a similar change in hemoglobin level was found after administration of one unit of packed red blood cells [38, 39]. The estimated blood loss is a significant measurement of quality of care even if the patient receives no blood transfusion.

A sufficient number of blood counts will be analyzed in order to acquire sufficient data. Meunier et al. described a decrease in hemoglobin level after a single major blood loss (due to the blood donation) even after 6 days [40]. Prospective data are also needed to answer questions about the timing and frequency of sampling after RARP [36].

Chan et al. proved that the results can be significantly affected by the weight of the prostate. A larger prostate could mean longer operating time and greater blood loss. Therefore, the results will be weighted for the grams of the prostatic tissue [41].

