### Sample size calculation

The sample size calculation is based on the data from our pilot study [29]. We used two-sample *T* tests allowing unequal variance with respect to the primary endpoint, which is the difference in hemoglobin level drop on postoperative day (POD) 1. The level of significance is set to 5 g. With *α* = 1% and *β* = 10%, a sample size of 64 patients per group is necessary to detect a clinically significant difference between the groups. With an expected dropout rate over 33%, we plan to enroll 200 patients in the study.

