### Data collection

A daily visit of the study patients will be made by clinical investigators or a delegated physician. All protocol-required information collected during the trial will be entered into the patient’s record form.

Patient identification on the case report form (CRF) is through their unique trial identifier, allocated at the time of recruitment. Data coding will be carried out at various stages during the study. The patient’s record form is subject to audit by the principal investigator (PI) and Institutional Review Board (IRB).

Preoperative data gathered include patient age, body mass index, American Society of Anesthesiologists physical status classification system score, and comorbidities. Intraoperative data to be collected include surgery duration (skin to skin), console time (console surgeon activity time), and weight of the prostate.

Laboratory tests will include blood cell count (BCC), hematocrit test, and plasmatic creatinine level at the beginning of the procedure, 3–6 h after the procedure, on POD 1, POD 2, and POD 7 in the morning.

The differences between the hematocrit and hemoglobin levels (eventually weighted for the grams of the prostatic tissue) and hemoglobin/creatinine ratios will be obtained.

The volume of the fluids in the drain will be measured on postoperative day 1, and if the volume does not exceed 200 ml for 24 h, the drain is extracted. If the volume will be higher than 200 ml/24 h and the creatinine level in the drain fluid exceeds 500 μmol/l, urinary leakage will be confirmed (29). Patients with confirmed urinary leakage or urinoma will be excluded from the evaluation.

Postoperative course assessments will include duration of intermediate/intensive care, hospital stay including readmissions for postoperative complications, reinterventions (reoperations, endoscopic and interventional radiology procedures), the reasons for readmissions, and transfusion rates. The patients will be seen by a clinical investigator 3 months after the surgery in an outpatient fashion. The evidence of complication and level of prostatic specific antigen (PSA) will be monitored. Upon completion of 200 patients, the statistical processing will be performed, and results will be unblinded.

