## Statistical methods

Each patient’s allocation to the analyzed population will be defined prior to the analysis and will be documented. In the full analysis set, patients will be analyzed as randomized according to the intention-to-treat principle. The intention-to-treat principle implies that the analysis includes all randomized patients. The per-protocol analysis set will include all the patients without major protocol deviation. Deviations from the protocol will be assessed as major or minor. Patients with major deviations from the protocol will be excluded from the protocol analysis. The safety analysis set will analyze the patients according to the treatment. The null hypothesis assumes that there is no difference in the hemoglobin level drop after the procedure in both groups. We will use a two-sample *T* tests allowing unequal variance with respect to the endpoint, which is the drop of hemoglobin levels. Differences between age and PSA will be assessed by the non-parametric Mann-Whitney *U* test. BMI and specimen weight will be compared by the Kolmogorov-Smirnov test. A *P*-value < 0.05 will be considered statistically significant. Statistical analyses will be performed using the NCSS statistical software (NCSS, Kaysville, UT, USA).

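### The part prostate weight plays in the haemoglobin analysis is stated inconsistently and never defined; one primary regression on baseline haemoglobin and prostate weight, reported in g/l, would settle it

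*Protocol article*

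**What the plan says.** Three sections of the protocol article deal with prostate weight and the haemoglobin result, each differently.

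- **Statistical methods.** The test is a two-sample t-test "allowing unequal variance with respect to the endpoint, which is the drop of hemoglobin levels". No covariate or weighting is named. Prostate weight appears only as a between-group comparison: "BMI and specimen weight will be compared by the Kolmogorov-Smirnov test".
- **Data collection.** Among the derived quantities are haematocrit and haemoglobin differences, "eventually weighted for the grams of the prostatic tissue". No rule says when this applies.
- **Discussion, Blood loss.** After arguing that a larger prostate can mean a longer operation and more bleeding, the article states without condition: "Therefore, the results will be weighted for the grams of the prostatic tissue".

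The design sections use the unweighted drop. Objectives and hypothesis compares the drop between groups. Sample size calculation names the endpoint, "which is the difference in hemoglobin level drop on postoperative day (POD) 1". Primary and secondary endpoints sets the clinically relevant difference at 10 g/l. Covariate-adjusted regression is mentioned only under Health economic analysis, for costs.

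**The concern.** A reader cannot tell from these sections what will be done with prostate weight. The word used could mean dividing each drop by grams, using grams as regression weights, or adjusting for weight as a covariate. These are different analyses with different estimates. The text does not say which results are covered, or whether the weighted result is the main one or a supporting one.

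Two things are at stake. First, an undefined second version of the haemoglobin result leaves room to choose between versions once the data are seen. Second, if drop per gram is meant, the unit becomes g/l per gram. A 20 g/l drop scores 20/25 = 0.80 with a 25 g prostate and 20/80 = 0.25 with an 80 g prostate (illustrative weights), so small glands carry most of the spread. The design target has no meaning on that scale.

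The plan also argues that weight affects blood loss, yet the only test it specifies uses neither weight nor baseline haemoglobin. Data collection lists both.

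**Working it through.** **1. The plan's own figure.** Sample size calculation states: "With *α* = 1% and *β* = 10%, a sample size of 64 patients per group is necessary". No SD is given, so 64 cannot be reproduced. It can only be solved for the SD it implies (two-sided test, normal approximation):

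SD = delta / [(2.576 + 1.282) × √(2/64)]

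- delta 10 g/l: 14.67 g/l
- delta 8 g/l (pilot difference, 25.6 − 17.6): 11.73 g/l
- delta 5 (the figure in the sample size section): 7.33 g/l

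The working case below is delta 10 with SD 14.67, for which 64 per group gives 90% power by construction.

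**2. If weighting means drop per gram.** Simulation used 64 per group, two-sided alpha 1%, 3,000 trials per setting, and a mean control drop of 25.6 g/l (pilot). Assumptions not in the document: log-normal specimen weight with mean 50 g and coefficient of variation 0.4, and the share of variance in the drop (R²) explained by weight and by baseline. The simulation standard error is about 0.5 points at 90% power, √(0.9 × 0.1/3,000), and 0.8 points at 70%. Power in %:

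| delta, SD (g/l) | R² weight / baseline | raw drop, Welch | drop per gram | regression on baseline and weight |
|---|---|---|---|---|
| 10, 14.66 | 0 / 0 | 89.8 | 70.1 | 89.2 |
| 10, 14.66 | 0.10 / 0.10 | 90.3 | 85.6 | 95.6 |
| 10, 14.66 | 0.20 / 0.10 | 89.6 | 91.2 | 97.2 |
| 8, 14.66 | 0 / 0 | 69.0 | 47.0 | 68.2 |
| 8, 14.66 | 0.20 / 0.10 | 67.7 | 70.0 | 84.4 |

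The per-gram version runs from about 20 points worse to about level. At delta 5 and SD 7.33 it gives 39–67% against about 90% for the raw drop.

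**3. Gain from baseline haemoglobin.** Let s0 and s1 be the SDs at baseline and postoperative day 1, and rho their correlation.

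- Change-score variance: s0² + s1² − 2·rho·s0·s1
- Baseline-adjusted variance: s1²(1 − rho²)
- With s0 = s1, the ratio is (1 + rho)/2

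With the change-score SD held at 14.67, alpha 1% and 64 per group, power is Φ(delta/SE − 2.576), where SE = 14.67 × √ratio × √(2/64):

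| rho (assumed) | variance ratio | n for 90% at 10 g/l | power at 10 g/l | power at 8 g/l |
|---|---|---|---|---|
| no adjustment | 1 | 64 | 90.0% | 69.5% |
| 0.8 | 0.90 | 58 | 93.2% | 75.1% |
| 0.5 | 0.75 | 48 | 97.0% | 83.8% |

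The Statistical methods section uses a different threshold, "A *P*-value < 0.05 will be considered statistically significant". At 5% the 8 g/l column becomes 87.0%, 90.2% and 94.6%.

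**4. When the gain vanishes.** The change score is already optimal if the slope of day 1 on baseline, rho × s1/s0, equals 1. With rho = 0.8 and s1 = 1.25·s0 (s0 = 1), the change-score variance is 1 + 1.5625 − 2 = 0.5625 and the adjusted variance is 1.5625 × 0.36 = 0.5625. The ratio is 1. The 0 / 0 rows above show the same: adjusting for two useless covariates leaves power unchanged within simulation error (89.2% against 89.8%).

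**The case against.** The strongest reply is that the plan does settle its primary analysis. The hypotheses, the sample size endpoint and the named test all use the unweighted drop. The firm sentence on weighting is Discussion text about results in general, and the Data collection sentence lists derived quantities. A reader might infer that the article declares two rival primary outcomes. It does not: nothing calls a weighted drop primary. Nor do both weighting statements hang on a later choice; the Discussion one is unconditional.

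A reader might also infer that the plan divides by grams. That is one reading only. Adjusting for weight would fit the wording too, and is close to what is proposed below. The per-gram power loss therefore depends on an unstated method, and is largest when weight has no bearing on the drop, contrary to the plan's own reason for weighting.

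Finally, a Welch t-test on change is valid under randomisation, and covariate choices are often left to an analysis plan. A smaller repair would also remove the contradiction: keep the t-test on the raw drop as primary and label one defined weight-adjusted analysis supportive.

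All of this stands as a limit on the claim. It does not remove the inconsistency, because the article itself commits to a weighting that its statistical section omits and no section defines.

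**Conclusion.** The point holds in a limited form. The use of prostate weight is absent in Statistical methods, loosely conditional in Data collection and firm in the Discussion, with no definition and no rank. The 10 g/l target and 64 per group support only the unweighted drop.

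If drop per gram were used, power would range from about 70% against 90% for the raw drop to about 91% against 90%, under the assumed weight distribution and an SD of 14.66 g/l. That SD is only what the stated sample size implies.

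Baseline adjustment lowers the variance by 10–25% for assumed rho of 0.8–0.5 with equal SDs, and may gain almost nothing otherwise. It would be wrong to read this as a guaranteed or cost-free power gain, since the document gives no SD, correlation, weight distribution or slope. The case for the regression is that it carries out the plan's own intention about weight on the g/l scale, uses data already collected, and loses nothing material in the worst case examined.

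The design is not invalidated. The separate conflicts over 5 g against 10 g/l and alpha 1% against 5% are not resolved by this change.

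**What to change.** Document the following before unblinding:

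1. **Primary analysis:** regression of postoperative day 1 haemoglobin (equivalently the drop, since baseline is in the model) on arm, baseline haemoglobin and prostate weight. Use a heteroscedasticity-robust standard error to keep the unequal-variance intent, and report the group difference in g/l.
2. **Sensitivity analysis:** the Welch t-test on the raw drop to postoperative day 1.
3. **Wording:** replace the weighting language in Data collection and in the Discussion with a statement that prostate weight enters as a covariate.
4. **Two short additions:** a rule for missing specimen weight, and a reason why a single intra-operative infusion cannot change specimen weight, which is measured after randomisation.

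No new data are needed, and the two extra degrees of freedom are negligible. Timing is the main constraint. Trial status expected the last patient by 1 February 2022, and unblinding follows completion of 200 patients, so the change must be dated and recorded as made before the allocation was opened.

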### Dose

The therapeutic concentration of tranexamic acid in plasma ranges from 5 to 10 mg/kg. After an intravenous dose of 10 mg/kg, plasma concentration was maintained for 3 h, but orthopedics proved to be inadequate. Based on the abovementioned literature, we decided to administer a single dose, corresponding to 20 mg/kg to all patients in the treatment group 1 at the beginning of the procedure.

### Complications

Although transfusion rates after open retropubic radical prostatectomy (RRP) are low - 3.4%, and robotic approach dropped the rate even lower to 0.8% [42], in our pilot study to 1.0% [29]. The safety of homologous transfusion has improved over time, but the possibility of having transfusion-related reactions or acquiring transfusion-transmitted diseases still remains [43]. Concerns have been raised about the possible relationship between the administration of blood derivatives and an increased risk of relapse of malignancy and tumor-specific mortality [44, 45]. At this moment, we are aware of only one retrospective study showing a poor correlation between postoperative hemoglobin assessment and transfusion requirement among patients undergoing minimally invasive radical prostatectomy [36]. Prospective data is lacking.

Radical prostatectomy is associated with a higher risk of thromboembolism. Open radical prostatectomy has a considerably higher risk of thromboembolic events (1.0—15.7%) compared to robotic (0.2–3.7%) and laparoscopic (0.4–6.0%) approaches [46]. Administration of antifibrinolytics, which potentially increase the risk of thromboembolism in laparoscopic surgery for pelvic malignancy, may seem too risky. According to the literature data from recent meta-analyses, no demonstration of an increased risk of thromboembolism following treatment with tranexamic acid was observed [27, 28].

## Conclusion

Despite the enormous development in robot-assisted radical prostatectomy over 25 years, improvement is still needed. One possibility is to implement the ERAS (early recovery after surgery) protocol in everyday practice. Each of the original 22 recommendations (for example, preoperative nutritional examination and nutritional preparation, intestinal preparation, fasting time, prevention of thromboembolism, antibiotic prophylaxis, decolonization of the skin, minimally invasive approach, prevention of hypothermia, intestinal prokinetics, etc.) does not significantly improve the postoperative results alone. The prophylactic use of tranexamic acid at the beginning of robotic-assisted prostatectomy could be another piece of this mosaic. Because strategies that lead to small improvements might be meaningful from a system perspective if they can be delivered easily, at low cost, and at a population level ([47].).

## Trial status

The RARPEX trial is recruiting patients under protocol version 1.0 since February 24, 2020. The last patient is expected to be recruited by February 1, 2022.

## Data Availability

The materials described in the manuscript, including all relevant raw data, will be freely available to any scientist wishing to use them for non-commercial purposes, without breaching participant confidentiality. The datasets used and analyzed during the current study will be available from the corresponding author on reasonable request. In the event of publications arising from such analyses, those responsible are required to provide the principal investigator with a copy of any intended manuscript for approval prior to submission. Dissemination policy: It is anticipated that the study findings will be published in national and international peer-reviewed journals and presented at national and international meetings and to appropriate patient groups, all of which will be led by the PI. Upon request, participants may receive a lay summary of the principal study findings. The most significant results will be communicated to the public through press releases, and a paper on the primary outcome and safety data will be published soon after analysis and review. An ongoing update of the trial is maintained on the website ClinicalTrials.gov.

## Abbreviations

AE: Adverse events
CRF: Case record form
BCC: Blood cell count
CRA: Clinical research associate;
CTCAE: Common Terminology Criteria for Adverse Events
CT scan: Computed tomography scan
DVT: Deep vein thrombosis
IRB: Institutional Review Board
LMWH: Low-molecular weight heparin
LRP: Laparoscopic radical prostatectomy
MRI: Magnetic resonance imaging
PE: Pulmonary embolism
PI: Principal investigator
POD: Postoperative day
RARP: Robot-assisted radical prostatectomy
RRP: Open retropubic radical prostatectomy
SAE: Serious adverse events
SUSAR: Suspected serious adverse reaction
VTE: Venous thromboembolism
